### Statistical analysis

The proportion of screened clients entering the study will be determined. T-tests and chi-square analyses will be conducted to determine if those who did not enrol in the study were systematically different from those who did. T-tests and chi-square analyses will also be conducted to determine if there were any significant differences between the treatment and control groups at baseline. For outcome analyses, both intention-to-treat (i.e. analyses include all randomised participants, regardless of protocol adherence) and per-protocol analyses (i.e. where the intervention group only includes participants who received at least one session) will be conducted. Categorical and continuous measures of outcome will be examined using mixed or marginal longitudinal models.

To evaluate treatment fidelity, 10 % of each therapist’s sessions will be rated for compliance with the treatment manual. Interim descriptive analyses will take place at each assessment stage (including the baseline assessment), to assist with the monitoring of data collection and data entry. These analyses will be conducted by the research officers, who will not have access to the treatment allocation variable. Final stage analyses will be carried out after completion of the 12 month follow-up.

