### Trial design

The Activate study is a parallel, single blind, superiority randomised controlled trial. Participants will be randomly assigned to receive either Activate (*n* = 100) or treatment as usual (TAU; *n* = 100), stratified by treatment modality (RR and OST). Treatment as usual is the comparator group, as it is clinically important to determine whether Activate adds any benefit in terms of improved depression symptomatology and reduced dependence symptoms, beyond that gained from usual care (i.e. RR or OST). Separate randomisation schedules will be used for the two treatment modalities. To reduce the risk of bias, minimisation, a dynamic random allocation technique, will be completed by someone independent of the research team using Minim-Py [48]. Gender and depression severity have been identified as significant prognostic factors and minimisation will ensure classification of participants with respect to these variables. Depression severity will be categorised according to BDI-II score, as mild (14–19), moderate (20–28) or severe (29–63) [49]. Minimisation has been shown to have both theoretical and practical validity, in particular it is considered an effective randomisation tool in clinical trials of small to moderate sample size (approximately, *N* = 200–400) with multiple prognostic factors to be considered [50–52].

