#### Intervention

The trial will use a modified version of the BATD-R manual (Activate), which involves 10 individual, weekly 60-min sessions, with a psychologist from the research team. The 10-session format allows for the inclusion of topics deemed important for the target population, and there is evidence that clinically significant improvements in depression symptoms can be achieved within this period [45]. The BATD-R manual was modified to include psychoeducation about the relationship between substance use and depression. To assist in establishing treatment goals in relation to their substance use, some motivational interviewing techniques were incorporated. Namely, this involved asking questions to elicit change talk, such as, ‘*What would you like to be different about your current situation?’* Other additions include the provision of a list of behavioural techniques for managing craving [65], and a simple breathing exercise. Given the high levels of psychiatric comorbidity among substance users in drug treatment [66, 67], self-soothing and grounding techniques have been included for managing emotional distress, and defusion exercises for the management of unhelpful thoughts. Participants may choose to withdraw from the intervention at any time, but will still be contacted for follow-up assessment, unless they have withdrawn from the study.

To encourage treatment attendance participants in Activate will receive a reminder call the day prior to each session to confirm their appointment for the following day and appointment times will be highly flexible throughout the treatment program, with the option to reschedule appointments if required. Therapists will keep logs of clients’ attendance at sessions.

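### The per-protocol analysis removes non-starters from the Activate arm only, so the comparison carries a selection bias whose direction and size the protocol cannot fix

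*Protocol article*

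**What the plan says.** The trial is described under Trial design as a superiority study: "The Activate study is a parallel, single blind, superiority randomised controlled trial". The Statistical analysis section plans two outcome analyses. The first is "both intention-to-treat (i.e. analyses include all randomised participants, regardless of protocol adherence". The second is "per-protocol analyses (i.e. where the intervention group only includes participants who received at least one session) will be conducted". The restriction is stated for the intervention group; no counterpart is stated for TAU, and none could be, because nobody in TAU is offered a session.

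The Intervention section describes a course that "involves 10 individual, weekly 60-min sessions, with a psychologist from the research team". It adds that "Therapists will keep logs of clients’ attendance at sessions", and that people who stop the intervention are still approached for follow-up unless they leave the study altogether.

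**The concern.** Randomisation makes the two arms alike in everything that precedes treatment, including the readiness to attend a first session. Removing those who do not attend from one arm breaks that balance. Activate is then represented by starters, and TAU by a mixture of people who would and would not have started. Any difference in prognosis between these two types enters the estimate as if it were an effect of treatment.

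The label adds a second, smaller problem. Someone who attends once has received 1/10 = 10% of the course. By the protocol's own session outline (Overview of treatment), Session One covers procedures, psychoeducation, rationale and behaviour monitoring, and activities are first scheduled in Session Four. A reader who sees a per-protocol result will assume much more exposure than the set guarantees.

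At stake is the reading of the second analysis. If it is more favourable than ITT, the excess could be selection alone.

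**Working it through.** The protocol gives no figure for this point, so there is none to reproduce. The check derives the bias and then illustrates its size.

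**Bias with no treatment effect.** Let *q* be the share of each arm that would not attend any session, and *g* the mean BDI-II outcome of these non-starters minus that of starters (positive = worse). Let μ be the mean for starters.

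- Expected TAU mean: (1 − *q*)μ + *q*(μ + *g*) = μ + *qg*
- Expected Activate mean after the exclusion: μ
- Expected difference, TAU minus Activate: *qg*
- Expected difference under ITT: (μ + *qg*) − (μ + *qg*) = 0

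**Inputs from the protocol (Sample size calculation):** BDI-II difference 5, SD 15, within-subject correlation 0.023, final sample 160, hence 80 per arm. Follow-ups at 3 and 12 months give two post-baseline measurements.

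**Inputs that are assumptions:** *q* from 5% to 30%; *g* from −5 to +10 points. The protocol states neither.

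**Standard error.** The mean of two follow-ups has variance factor (1 + 0.023)/2 = 0.5115, so its SD is 15 × √0.5115 = 10.73. After the exclusion, SE = 10.73 × √(1/[80(1 − *q*)] + 1/80). At *q* = 20% this is 10.73 × √(1/64 + 1/80) = 1.80.

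**False-positive rate** (two-sided 5%, normal approximation, with *b* = *qg*): 1 − Φ(1.96 − *b*/SE) + Φ(−1.96 − *b*/SE). At *q* = 20%, *g* = 5: *b*/SE = 1.00/1.80 = 0.56, giving 8.6%.

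| *q* | bias, *g* = 5 | false positives | bias, *g* = 10 | false positives |
|---|---|---|---|---|
| 5% | 0.25 | 5.2% | 0.5 | 6.0% |
| 10% | 0.50 | 5.9% | 1.0 | 8.8% |
| 20% | 1.00 | 8.6% | 2.0 | 19.9% |
| 30% | 1.50 | 12.6% | 3.0 | 36.1% |

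Against the planned 5-point difference, the bias runs from 0.25/5 = 5% to 3.0/5 = 60%. With *g* = 0 the bias is zero and the rate is 5% at every *q*. With *g* = −5 the bias is −0.25 to −1.50 points, against Activate.

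A simulation of 20,000 trials with no effect, *q* = 20% and *g* = 5 gave a mean difference of 1.00 for the restricted comparison and 0.00 for ITT.

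**Price of the alternative.** If nobody in TAU receives Activate, the complier-average effect is the ITT difference divided by (1 − *q*), and its SE is roughly the ITT SE divided by (1 − *q*). The ITT SE is 10.73 × √(2/80) = 1.70.

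- At *q* = 5%: 1.70/0.95 = 1.79, against 1.72 for the restricted comparison, about 4% wider.
- At *q* = 20%: 1.70/0.80 = 2.12, against 1.80, about 18% wider.
- At *q* = 30%: 1.70/0.70 = 2.42, against 1.87, about 30% wider.

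**The case against.** The strongest reply is that the planned ITT analysis covers everyone randomised, is listed first and is untouched by the exclusion. The protocol supports it by following up those who leave therapy. That stands: the defect lies in the second analysis only.

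Three stronger readings are tempting, and the protocol does not support them.

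- *The bias is known to favour Activate.* A reader might infer this because people who never start therapy in a substance-use sample may well be doing worse. That is plausible, but the protocol gives no non-start rate and no prognosis for non-starters. Reminder calls and flexible appointments are meant to keep the share low. If non-starters are also harder to trace, their share among those with outcome data may be lower still, in both arms.
- *The set says nothing about treatment received.* It does separate some treatment from none. What it does not show is adequate exposure. Raising the session threshold would not cure the selection: it would remove more people from one arm and could enlarge the bias.
- *The plan lets a superiority claim rest on the per-protocol result.* Nothing in the protocol says so. Which analysis decides is commonly settled in a statistical analysis plan, which is not at hand, so silence on this is not a fault of the article.

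It can also be said that a complier-average estimate is not the only acceptable remedy and brings an untestable assumption of its own. That is true. Labelling the starters analysis as supportive would meet part of the concern, but it would leave a biased estimator in place.

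**Conclusion.** The concern holds for the per-protocol comparison as the Statistical analysis section defines it. A post-randomisation exclusion in one arm gives a selection bias equal to the non-starter share times the prognostic gap. This follows from the definition and needs no outside figure.

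Direction and size cannot be determined from the protocol. The 0.25 to 3.0 points, and the false-positive rates of about 5% to 36%, rest on assumed shares of 5–30% and gaps of 5–10 points. They also rest on 80 evaluable participants per arm, two follow-ups and the protocol's SD and correlation. They show what the method can do, not what will happen in this trial.

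The name is a separate, lesser point: one session of ten defines treatment starters, not participants treated per protocol.

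**What to change.** - Rename the set *treatment starters*.
- State that the superiority conclusion rests on the ITT analysis.
- Replace the one-arm-restricted comparison with a complier-average causal effect estimate, labelled supportive. Randomisation is the instrument, and the exposure is having started therapy, taken from the therapists' attendance logs. Using the same one-session threshold here is consistent, because the fault lies in the one-sided comparison and the label, not in the threshold. Delivery by project therapists, chosen to limit contamination of TAU, makes it reasonable to expect almost no crossover into Activate.
- Treat any version based on the number of sessions attended as exploratory, because it needs stronger assumptions.

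No new data are needed: attendance is already logged and those who leave therapy are already followed up. The cost is some wording, one additional model, an interval roughly 4% to 30% wider over the assumed range of non-start, and an exclusion restriction that cannot be tested. The restriction says that being allocated to Activate does not change the outcome of someone who never attends.

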#### Dissemination of results

The research team intend presenting the findings of this trial at professional seminars, national and international conferences, and in manuscripts submitted for publication in peer-reviewed journals. Results will also be reported to the UNSW and Northern Sydney Local Health District HRECs. Only aggregated group data will be reported and no individuals will be identified.

## Discussion

This protocol presents the design of the Activate study, a randomised controlled trial, which seeks to evaluate the efficacy of a modified version of BATD-R (Activate) among individuals in treatment for SUDs. The primary aim of the study is to investigate the efficacy of the Activate intervention in comparison to treatment as usual, in reducing symptoms of depression and substance dependence. For the Activate intervention group, treatment retention, client compliance, and client satisfaction will be assessed. The secondary aim of the study is to examine whether other factors, including those associated with therapy (environmental reward, behavioural activation), and those concerned with mental health (anxiety and social phobia, borderline personality disorder, traumatic events, rumination, distress tolerance, and sleep), impact upon the Activate treatment response.

### Strengths and limitations

A strength of the Activate study is that it is the first randomised controlled trial to evaluate the efficacy of behavioural activation therapy for depression among individuals in both inpatient and outpatient substance abuse treatment settings, and in an individual format. Follow-up assessments will occur at 3- and 12-months post-baseline in both the Activate intervention group and the control (TAU) group, which will provide an opportunity to evaluate the long-term effects of Activate among this population for the first time. Primary outcomes of severity of depression and dependence will be assessed by research officers who will be blind to treatment allocation, using validated measures. The incorporation of some motivational interviewing techniques, a brief relaxation strategy, and psychoeducation about the role of substance use in depression targets the intervention more specifically for substance users. Defusion exercises, self-soothing and grounding techniques have been included to equip participants with skills for managing rumination and emotional distress, which are prevalent among this group [68], so they can attend to the BATD-R protocol more fully.

One limitation of the Activate study is excluding individuals who have active suicidality, self-harm or psychosis, and those who report organic or traumatic brain injury. This may be considered to reduce the generalisability of results to a real world sample. However, these exclusion criteria were based on the individual’s likely inability to effectively engage with, and thus benefit from the type of intervention offered. A potential challenge for the study will be retaining participants, as individuals with SUDs are traditionally very difficult to follow-up. To maximise follow-up rates, research officers will build good rapport with participants, obtain detailed contact information to help with locating participants, reinforce to participants the importance of conducting follow-ups, and financially compensate participants for the time required to complete the interviews (AU$30). These methods have been utilised in previous studies among substance users, which achieved commendable 12-month follow-up rates of around 80 % [20, 69].

## Conclusion

Integrated treatment is recommended in people with psychiatric illness comorbid with substance use problems. Yet, there are currently few evidence based treatment options for co-occurring depression and SUD. BATD-R is a manualised treatment that has shown promise among drug and alcohol residential rehabilitation clients [31, 44] and among psychiatric inpatients [46], but larger, longer term trials are needed to broaden the BATD-R evidence base. The Activate study will be one of the few randomised controlled trials of psychosocial treatments for this comorbidity to be conducted internationally. The findings are likely to contribute significantly to understanding the types of programs that are effective in treating this comorbidity.

## Abbreviations

ATOS, Australian Treatment Outcome Study; AUC, Area under the receiver operator curve; AU$, Australian dollars; AUDIT, Alcohol Use Disorders Identification Test; BADS-SF, Behavioral Activation for Depression Scale Short Form; BAI, Beck Anxiety Inventory; BATD, Behavioural Activation for Depression; BATD-R, Behavioral Activation for Depression: Revised Treatment Manual; BDI-II, Beck Depression Inventory-II; CIDI 3.0, Composite International Diagnostic Interview version 3.0; CSQ-8, Client Satisfaction Questionnaire; DSM-IV, Diagnostic and Statistical Manual of Mental Disorders-Fourth Edition; DTS, Distress Tolerance Scale; EROS, Environmental Rewards Observation Scale; HREC, Human Research Ethics Committee; IPDE, International Personality Disorders Examination; NHMRC, National Health and Medical Research Council of Australia; OST, Opioid Substitution Therapy; PCL-C, Posttraumatic Stress Disorder Checklist – Civilian Version; PHQ-9, Nine Item Patient Health Questionnaire; PTQ, Perseverative Thinking Questionnaire; PTSD, Post-Traumatic Stress Disorder; RR, Residential Rehabilitation; SCID, Structured Clinical Interview for DSM disorders; SDS, Severity of Dependence Scale; SF-12, Short Form-12 Health Survey; SMAST, Short Michigan Alcohol Screening Test; WHO, World Health Organization.
